#### Other Assessments

*Personality*: personality traits will be assessed with the 10 Item Big Five Inventory (BFI-10). The BFI-10 is a short scale to assess the five-factor model as the predominant model for describing personality along the dimensions openness to experience, conscientiousness, extraversion, agreeableness, and neuroticism. The BFI-10 has shown satisfactory psychometric properties (95).

*Optimism/pessimism*: optimisim/pessimism is defined as expectations toward future events in all life domains, with “optimists” having the expectation that mostly good things will happen and “pessimists” having the expectation that mostly bad things will happen. The personality trait optimisim/pessimism will be assessed with the scale Optimism-Pessimism-2 (SOP2). The SOP2 has been validated among the general population and has shown good reliability and validity (96).

*Social support*: the Oslo 3-items social support scale (OSS-3) will be used to measure the extent of available social support. The OSS-3 has been developed as part of a large-scale mental health survey and has been used in European comparative research, where its feasibility and predictive validity with respect to mental health has been confirmed (97).

*Socio-demographics*: core social variables (age, gender, nationality, ethnicity, income, employment status, marriage/relationship status, and education) will be collected on the basis of the recommended measures from the Federal Statistical Office (98).

*Patient history*: past and current intake of medication for mental-health problems, and past use of psychotherapy and similar health services will be assessed. Past use of health services will assess the number and duration of health service usage.

### Statistical Analysis

Before analysis, data will be prepared and cleaned according to the guidance in Ref. (99). Data will then be analyzed according to the recommendations in the CONSORT statement for evaluation of e-health interventions, as well as the mHealth evidence reporting and assessment checklist from the WHO mHealth Technical Evidence Review Group (100, 101). Intention-to-treat analysis (ITT) and additional per-protocol analysis (PP) will be performed, the former including the data of all participants randomized and the latter using only the subset of participants who complete all assessments (T0, T1, T2, T3).

Multilevel models are an appropriate data-analytic strategy for smartphone data, involving daily measurements, resulting in repeated observations nested within individuals (102). These models are well suited to test the general effectiveness of supported monitoring among smartphone users, but also its differential effectiveness and its conditional effectiveness. Models include analysis of both within-person and between-person variance. Missing data will be replaced using Markov Chain Monte Carlo multiple imputation, which is considered to produce more precise estimates of the true intervention in the ITT analysis compared other imputation methods, i.e., last observation carried forward (103).

*General effectiveness*: to test for changes in the outcome variable from before to after the intervention period, repeated-measures analysis of variance (RM-ANOVA) will be conducted for each intervention outcome (104). In the RM-ANOVA, the within-person effect of time is used as an index of general intervention effectiveness. For the analysis of between-person variance, the model can be extended to multivariate analysis of variance (MANOVA). In this case, a between-subjects factor for group membership is added (Supported monitoring group vs. AA group vs. control group). If there is an interaction between the time factor and the group factor, we will conclude that the intervention was effective.

*Differential effectiveness*: to examine person-level moderators of the intervention effect, a between-person factor is added to the MANOVA. This results in a three-way interaction (person factor × time × group). However, as only categorical person variables can be included in the MANOVA, multivariate multilevel models for fixed occasions will also be performed to allow for continuous variables as moderators (105). The between-person moderators to be included in the analysis of differential effectiveness include gender, age, and baseline distress severity (low, moderate, high).

Conditional effectiveness: to examine whether time-varying characteristics of the situation (e.g., days spent at work) or the individual (e.g., being physically active) might moderate the intervention effect, multivariate multilevel models will be extended with a continuous or categorical day-level variable. To estimate the pure within-person effect of the time-varying moderator, continuous day-level variables will be centered on the person-mean.

*Effect sizes*: Cohen’s *d* will be calculated as a measure of the effect size, where *d* = 0.8 or more is classified as a large effect, *d* = 0.5–0.8 is classified as a moderate effect, and *d* = 0.2–0.5 is classified as a small effect. According to Feingold (106), the raw score standard deviation of the outcome variable at baseline assessment will be used to compute Cohen’s *d*.

*Treatment response*: changes in mental health on an individual level will be examined with the widely used Reliable Change Index (RCI) by Jacobson and Truax (107). Participants with an RCI greater than 1.96 will be classified as “responders,” and those with an RCI below −1.96 will be classified as “deteriorated.” To assess the average number of persons who need to be treated to prevent one additional bad outcome, the number needed-to-treat (NNT) will be calculated. Additionally, the number-needed-to-harm (NNH) will be calculated, indicating the number of responders in the intervention group for one extra person to have a symptom deterioration. To set the benefits of the intervention in relation to its risk, the benefit-risk ratio will be calculated by dividing the NNT through the NNH (108).

*Daily life data*: we will compute Cox proportional hazards models to investigate daily life behavior as risk and protective factors of mental health. Cox proportional hazards models are a type of survival model that allows for the estimation of the hazard (or risk) of an event of interest given prognostic variables. We will model changes in mental health as measured by K6 as the outcome event (i.e., improved, maintained, and deteriorated), and separate models will be computed for well-being, intentions to seek help, and help-seeking behavior as outcome event. As risk and protective factors, we will include daily life measures. Risk factors include alcohol and substance use, the frequency of daily hassles, low social activity, and low physical activity. Protective factors include coping behavior, social support, and physical activity. Furthermore, the instability or variability of daily symptoms over the 30-day monitoring period will also be examined as a risk factor by computing within-person variances, first-order autocorrelation, the mean square successive differences, and the probability of acute change according to Jahng et al. (109). Discrimination ability (the ability of the model to separate individuals who develop the event from those who do not) will be assessed with the C statistic. Model calibration, that measure how accurately model predictions match overall observed event rates, will be evaluated with a version of the goodness of fit (110). Internal model validation will be carried out. For all daily life analysis, data from the AA group will be used (*N* = 62).

*Access*: we will describe access to the intervention in terms of population characteristics (sample representativeness), demographics, clinical characteristics, and sample comorbidities using the appropriate descriptive statistics.

*Engagement*: to assess participant engagement, we will examine the proportion of study drop-outs and the proportion of enrolled individuals who respond to the outcome assessments at each time point, and the proportion of daily life assessments filled out during the 30-day interval.

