#### Sample Size Calculation

A power analysis was performed to detect a group difference on the primary outcome at post-assessment group. The calculation is based on the assumption that a difference between the supported monitoring group and either AA group or control group within the margin −0.25 < Cohen’s *d* < 0.25 can be neglected. We assume no difference between the two latter groups. Therefore, a between-group difference of *d* = 0.25 should reach statistical significance as an indicator of the general effectiveness of the intervention. The target sample size was computed using Gpower (40) for a repeated-measures analysis of variance for a within-between interaction of time and group (ANOVA). We used a targeted power of 95%, a significance level alpha of 0.05, four assessment waves, a conservative estimate of correlation between measurements (*r* = 65) and variances of the differences between groups (non-sphericity correction epsilon = 0.8). This results in a total *N* = 141. Adding 20% drop-out at T2 and T3, we will include 186 participants (62 per group).

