**Figure 1 F1:**
[figure not shown]
Study flow.

Three equally sized distress groups are formed, with inclusion probabilities according to prevalence estimates for the Kessler K6 screening scale (32). To achieve equally sized distress groups, participants with moderate to high distress will be over sampled. To approximate representativeness for the general adult population from 18 to 45 years, quotas for age and gender are defined according to the distribution of the latest Zensus population survey (36). Stratification by age is important to account for differential smartphone usage by age, with younger people having a higher rate of smartphone usage as compared to older people. Three age groups will be formed: Young (18–26, 29,5%), Middle (27–35, 30,1%), and Older (36–45, 40,5%). Due to a higher prevalence of mental health problems among women, groups will also be stratified by gender (49.8% male, 50.2% female).

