### Outcomes

Study outcomes are assessed at four time points: screening (T0), baseline (T1), post-assessment (T3) and follow-up (T4). While the screening (T0) relies on self-assessments collected during participant registration on the study website, structured telephone interviews are conducted at T1, T2, and T3 to assess the primary outcome. The telephone interviews will be conducted by the Academic Survey Lab at the University of Hamburg. Trained interviewers who are blinded to the study condition will conduct the interviews, resulting in an independent outcome assessment to avoid confounding with the self-monitoring data. The secondary outcomes will be self-assessed on the smartphone for all three groups.

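### The primary time-by-group RM-ANOVA uses pre-treatment K6 only as an outcome level; adjusting for it as a covariate would be a nearly free gain in precision of uncertain size

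*Protocol article*

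**What the plan says.** Under Statistical Analysis (General effectiveness), each outcome is tested by RM-ANOVA. A group factor is then added: "In this case, a between-subjects factor for group membership is added (Supported monitoring group vs. AA group vs. control group"). A time-by-group interaction is taken as proof that the intervention works. The same section mentions multilevel models as suited to general effectiveness but names no covariates for them. Baseline distress severity, age and gender appear only as moderators, under Differential effectiveness.

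The Sample Size Calculation sizes the same test, a "repeated-measures analysis of variance for a within-between interaction of time and group (ANOVA"), with "four assessment waves, a conservative estimate of correlation between measurements".

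The Outcomes section gives the timing: "Study outcomes are assessed at four time points: screening (T0), baseline (T1), post-assessment (T3) and follow-up (T4"). It then says that T0 is self-assessed on the website and that telephone interviews at T1, T2 and T3 measure the primary outcome. The labels for the two later visits differ within that section. Here T2 means the 4-week post-assessment and T3 the 12-week follow-up, as in the per-protocol definition. The K6 also forms the distress groups, so a K6 score must exist at screening.

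**The concern.** K6 is measured twice before treatment, and those scores should predict the post-treatment score well. A time-by-group interaction uses them by subtraction, which imposes a slope of 1 on baseline. Under the plan's own correlation the expected slope on a single baseline is 0.65. Subtraction therefore leaves avoidable noise in the comparison and over-corrects a chance baseline imbalance. Recruiting three equally sized distress groups widens the spread of K6 scores, and with 62 per arm some imbalance is possible.

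If the model really has four waves, its interaction has (3 − 1)(4 − 1) = 6 numerator degrees of freedom. Two of them compare the arms on T1 minus T0, where no treatment effect can exist. What is at stake is precision in the main comparison, not bias.

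**Working it through.** **Inputs.** From the Sample Size Calculation: "We used a targeted power of 95%, a significance level alpha of 0.05, four assessment waves"; "a between-group difference of *d* = 0.25 should reach statistical significance"; "a conservative estimate of correlation between measurements (*r* = 65"), read as r = 0.65; epsilon 0.8; N = 141 evaluable (n = 47 per arm) and 186 enrolled (n = 62); no difference between the two controls. Assumed here: equal variances (SD 1), equal correlation between all waves, T1 taken before treatment starts, and no dropout within each N shown.

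**1. The plan's own figure.** For the interaction, λ = f²·N·m·ε/(1 − r), with df (k − 1)(m − 1)ε and (N − k)(m − 1)ε. Put in k = 3, m = 4, ε = 0.8 and f = d/2 = 0.125. At N = 141, λ = 0.015625 × 141 × 4 × 0.8/0.35 = 20.14 and power is 95.3%. The minimum is N = 140, or 141 for equal arms, so the plan's figure reproduces. The article does not print f; it is inferred because it gives this N.

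**2. Variance per person at 4 weeks.**

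| Use of baseline | Formula | r = 0.65 | r = 0.5 | r = 0.8 |
|---|---|---|---|---|
| Change from T1 | 2(1 − r) | 0.700 | 1.000 | 0.400 |
| Adjusted for T1 | 1 − r² | 0.578 | 0.750 | 0.360 |
| Adjusted for T0 and T1 | 1 − 2r²/(1 + r) | 0.488 | 0.667 | 0.289 |

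Change from the mean of T0 and T1 has variance 1 − 2r + (1 + r)/2 = 0.525 at r = 0.65.

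**3. Power of the planned interaction at a literal d = 0.25 in the supported arm.** λ = n·(2/3)·d²·S·ε/(1 − r). S is the sum of squares of the centred time pattern: 1 for four waves with the effect at T2 and T3, 0.75 for four waves with the effect at T2 only, and 2/3 for three waves under either pattern.

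| Model | N = 141 | N = 186 |
|---|---|---|
| Four waves, effect at T2 and T3, ε = 1 | 37.0% | 48.7% |
| Four waves, effect at T2 and T3, ε = 0.8 | 32.6% | 42.8% |
| Four waves, effect at T2 only, ε = 1 | 27.9% | 36.8% |
| Four waves, effect at T2 only, ε = 0.8 | 24.7% | 32.4% |
| Three waves (T1 to T3), ε = 1 | 29.5% | 38.5% |

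Both values of ε are shown because the plan uses 0.8, whereas equal variances and correlations imply 1.

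**4. Power of a three-group test on the 4-week K6.** λ = n·d²·(2/3)/variance, with 2 numerator df. For T0 and T1 adjustment at n = 47, λ = 47 × 0.0625 × (2/3)/0.488 = 4.01.

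| Analysis of 4-week K6 | N = 141 | N = 186 |
|---|---|---|
| Change from T1 | 29.6% | 38.1% |
| Adjusted for T1 | 35.2% | 45.2% |
| Change from mean of T0 and T1 | 38.3% | 49.0% |
| Adjusted for T0 and T1 | 40.9% | 52.1% |

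Simulation agrees to within about 1.5 points.

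**5. The gain.**
- Against the four-wave interaction, the smallest gains are 40.9 − 37.0 = 3.9 and 52.1 − 48.7 = 3.4 points. The largest are 40.9 − 24.7 = 16.2 and 52.1 − 32.4 = 19.7.
- Against three waves: 40.9 − 29.5 = 11.4 and 52.1 − 38.5 = 13.6.
- Covariate adjustment alone (same contrast, both baselines used in each): 40.9 − 38.3 = 2.6 and 52.1 − 49.0 = 3.1. For the mean of T2 and T3, with the effect at both, power goes from 54.3% to 59.3% and from 67.3% to 72.4%, about 5 points.

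**6. At the effect that reproduces N = 141.** For four waves f² = d²/18 if the effect is at T2 and T3, or d²/24 if at T2 only. So f = 0.125 means d = 0.125 × √18 = 0.53 or 0.125 × √24 = 0.61. Simulated power of the four-wave RM-ANOVA is then 97% to 99.6%, and adjusting the 4-week score for T0 and T1 changes it by about −1 to +2 points.

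**The case against.** The strongest reply is that a time-by-group RM-ANOVA in randomised arms is valid, that covariate lists are often left to an analysis plan that is not shown here, and that the gain is modest. Validity stands: a reader might infer that the primary result would be biased, and nothing in the document supports that. The second part does not stand, because the article names its primary model, its only between-subjects factor and its success rule. The third part is partly right, and it limits the claim in four ways.

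- **A fixed loss of 6 to 14 points.** A reader could get this range by comparing change from T1 (29.6% / 38.1%) with adjustment for T1 or for both baselines (35.2% to 40.9% / 45.2% to 52.1%). The three-wave interaction has nearly the same power as that change score. But change from T1 is not the four-wave test that was sized. With ε = 1 and an effect lasting to follow-up, that test (37.0% / 48.7%) even beats adjustment for T1 alone.
- **T0 as an outcome wave.** This is inferred from the four waves in the sample size section and from the per-protocol definition. The Outcomes section can be read as T1 to T3 only, and then the wasted 2 of 6 degrees of freedom disappear.
- **The cause of the loss.** Much of the larger figure comes from the omnibus interaction and from how the two baselines are used, not from missing covariate adjustment.
- **Age and gender.** They define recruitment quotas ("quotas for age and gender are defined according to the distribution of the latest Zensus population survey") and are not stated as randomisation strata. No gain from adjusting for them has been shown.

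**Conclusion.** The point holds as a recommended improvement in efficiency. The planned test uses pre-treatment K6 less well than it could, and at a true difference of d = 0.25 the total gain available is about 3 to 20 points of power, of which about 3 to 5 come from covariate adjustment alone. This rests on r = 0.65, equal correlations between waves, equal controls and d read as a literal post-treatment difference. The T0 correlation is the least certain input, because T0 is collected on the web and is used to select participants, whereas the later scores come from interviews.

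The variance ordering does not depend on r: for any r between 0 and 1, adjusting for T1 beats subtracting it, and adding T0 helps further. At the effect that reproduces the plan's sample size the gain is negligible. A reader might also infer that adjustment rescues the stated power. It does not: at d = 0.25 power stays at 41% to 52%, far from 95%. That gap is a separate sample size question.

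**What to change.** Make the primary analysis a mixed model of post-treatment K6, with the 4-week and 12-week scores as outcomes. Include group, time and group-by-time, and enter T1 K6 and T0 K6 as continuous covariates. Read the supported-versus-control difference at 4 weeks, which is the comparison the sample size section says it targets. Keep the RM-ANOVA as a sensitivity analysis, and state whether it uses three or four waves. Adding age and gender is optional.

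The cost is a change of wording in the Statistical Analysis section. Both K6 scores are already collected, no participants or visits are added, and the trial is still in preparation, so no data constrain the choice.

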Whether supportive monitoring can be safely applied in unsupervised settings has not yet been sufficiently documented. Besides technical challenges (e.g., battery problems, availability of internet connection), issues of data security and data privacy are critical. As continuous self-monitoring is likely challenging, especially for person with mental-health symptoms, various factors such as low motivation and energy, the tolerability and desirability from the patients’ perspective need to be examined. It is also unclear which subgroups of patients mostly benefit from this type of intervention. Also, the identification and timely management of crises and risk of harm during self-monitoring must be considered. Several trials have shown negative results, including more sustained symptoms as a result of self-monitoring mental health (30). This indicates that self-monitoring needs in-depth consideration and clarification before it is implemented as a clinical tool in the future.

Before this background, we aim to develop and evaluate to the best of our knowledge the first mHealth intervention for mental health on the basis of supportive self-monitoring in the general population. A field test of mental health self-monitoring in the general population has been conducted previously and serves as the basis of this project (31). Building on a smartphone application for Android devices, the mHealth intervention can be disseminated at low cost, and can achieve broad accessibility in the population. Implementing an indicated prevention approach, we want to focus on adults from the general population with psychological distress, who display lowered productivity in day-to-day activities, but who are not seeking professional help. Examining the intervention across subgroups, subjects with low, moderate and high mental distress will be included, covering all degrees of mental-health problems. As smartphones are increasingly used not only by young people, but across all age groups, the study will include young and middle aged adults aged 18–45. We hypothesize that by using the intervention, participant’s mental health and health-related behaviors will improve.

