## Material and Equipment

### Stepwise Procedures

A fully mobile 3-arm RCT will be conducted. The intervention will be compared toward AAs (self-monitoring without support) and a passive control group (no self-monitoring and no support). We hypothesize that using the intervention will improve mental health as compared to the control groups, where we expect no significant changes. The RCT will be registered prospectively as a clinical trial in the German registry for clinical trials (Deutsches Register Klinischer Studien).

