#### Control Groups

The intervention will be compared to two control groups: first, the active control group will complete daily AAs (self-monitoring without support). Second, there will be a passive control group (no self-monitoring and no intervention).

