#### Secondary Outcomes

*Well-being*: the last item from the EUROQOL EQ-5D will be used to measure well-being (86). Participants are asked to rate their well-being on a Likert scale ranging from 0 to 100, where 0 represents the worst state and 100 the best state: “*What number between 0 and 100 best describes your well-being today?*”

*Intentions toward help-seeking*: The intention to seek help for a mental health problem will be measured with the General Help-Seeking Questionnaire (GHSQ) (87). The GHSQ asks: “*If you were having a mental health problem, how likely is it that you would seek help from the following source?”* with two help source options: 1. informal source (friend or family) and 2. professional source (general practitioner, mental health service, educational health service). Respondents rate the likelihood of seeking help from each source on a 7-point Likert scale ranging from “extremely unlikely” to “extremely likely.”

*Help-seeking behavior*: help-seeking is defined as the behavior of actively seeking assistance, regardless of whether the source is informal or formal. The Actual Help-Seeking Questionnaire (AHSQ) will be used to measure help-seeking for a mental health problem within the past 4 weeks (88). The AHSQ first asks whether or not any help had been sought for a mental health problem during the reference period. Second, if help had been sought, whether it was sought from an informal source or from a professional source (identical to the help source options of the GHSQ). For each item, a score of one indicates that help had been sought and a score of 0 that help had not been sought.

*User activation*: we refer to user activation as the degree of perceived knowledge, skill, and confidence for the active self-management of one’s mental health condition. The Patient Activation Measure (PAM) will be used, a reliable and validated measure for the degree of activation. The PAM rates the agreement to 13 items on a 4-point scale (89). Respondents are scored on four levels, with a higher score indicating higher activation.

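### The success rule accepts any time-by-group interaction across three arms, so worsening in the self-monitoring control, or in the supported arm itself, would count as effectiveness

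*Protocol article*

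**What the plan says.** Under general effectiveness, the Statistical Analysis section prescribes a repeated-measures ANOVA for each outcome. It adds a between-subjects factor with three levels, "Supported monitoring group vs. AA group vs. control group", and then states the rule: "If there is an interaction between the time factor and the group factor, we will conclude that the intervention was effective". The same paragraph also treats the effect of time alone as an index of effectiveness, which is not a comparison between arms.

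Elsewhere the aim is directional and comparative. Stepwise Procedures: "We hypothesize that using the intervention will improve mental health as compared to the control groups, where we expect no significant changes". Anticipated Results repeats this. The Sample Size Calculation refers to a difference at one time point, "A power analysis was performed to detect a group difference on the primary outcome at post-assessment group", and says of the AA and passive arms: "We assume no difference between the two latter groups". The Introduction warns: "Several trials have shown negative results, including more sustained symptoms as a result of self-monitoring mental health (30". Daily self-monitoring without support is exactly what the AA arm receives (Control Groups).

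**The concern.** An omnibus interaction over three arms shows only that the profiles over time are not parallel. It does not show which arm departs from the others, or in which direction. Three quite different situations satisfy the rule: the supported arm improves, the supported arm worsens, or the AA arm worsens while the supported arm does no better than no treatment. Only the first matches the hypothesis.

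The third is not far-fetched on the article's own account, since it cites trials in which self-monitoring prolonged symptoms. The assumption that the two controls do not differ is made for sample size and is not checked by the rule. At stake is the trial's headline conclusion, because this sentence alone decides it.

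**Working it through.** **1. The plan's own figure.** Inputs from Sample Size Calculation: d = 0.25, so f = d/2 = 0.125; 3 groups; 4 waves; correlation 0.65 (printed as 65); epsilon 0.8; alpha 0.05.

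- λ = f² × N × m × ε/(1 − ρ) = 0.125² × 141 × 4 × 0.8/0.35 = 20.14
- df1 = (3 − 1)(4 − 1) × 0.8 = 4.8; df2 = (141 − 3)(4 − 1) × 0.8 = 331.2
- Power = 0.953, and 141 is the smallest total in equal groups that reaches 95%.

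The stated N = 141 is reproduced. The trial is thus sized on the same undirected test that serves as the success rule.

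**2. How often the rule declares effectiveness without benefit.** Assume that only the AA arm worsens, by d at post-assessment and follow-up, and that supported equals passive. The size of d is an assumption.

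- SD across arms of (1, 0, 0) = 0.471. SD across waves of (0, 0, 1, 1) = 0.5, or of (0, 1, 1) = 0.471.
- f = 0.471 × 0.5 × d = 0.236d with four waves; f = 0.471 × 0.471 × d = 0.222d with three.
- Example, d = 0.4, four waves, N = 141: f = 0.0943; λ = 0.0943² × 141 × 4 × ε/0.35 = 11.46 (ε = 0.8) or 14.32 (ε = 1); probability 74% or 82%.

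Both wave counts are shown because Sample Size Calculation uses four waves, while Outcomes assigns the primary-outcome interviews to T1, T2 and T3.

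| Worsening, AA only | Waves | N = 141 | N = 186 |
|---|---|---|---|
| 0.25 SD | 4 | 33–37% | 43–49% |
| 0.25 SD | 3 | 26–29% | 34–39% |
| 0.4 SD | 4 | 74–82% | 87–92% |
| 0.4 SD | 3 | 61–68% | 75–82% |

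The lower figure in each cell uses ε = 0.8, the upper ε = 1. The N = 186 column assumes no dropout. The 0.25 rows lie far below 95% because a shift of 0.25 in one arm at two of four waves gives f = 0.059, not the 0.125 entered in the plan.

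Nothing in f depends on which arm moves or in which direction. A simulation at 62 per arm, four waves and 0.4 SD (4,000 trials per scenario) confirms this: effectiveness is declared in 92% of trials when AA worsens, 92% when the supported arm worsens and 93% under true benefit.

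**3. Which replacement rule cures this.** With baseline K6 as covariate the residual variance is 1 − 0.65² = 0.5775, against 2(1 − 0.65) = 0.70 for a change score. The standard error of a pairwise contrast is √(2 × 0.5775/n) = 0.157 (n = 47) or 0.136 (n = 62).

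- *Credit for either contrast with Holm.* In the same scenario at d = 0.4, supported vs AA passes the first step (two-sided 0.025) with probability Φ(2.55 − 2.24) = 62% at 47 per arm and Φ(2.93 − 2.24) = 75% at 62. AA deterioration would still be credited.
- *Both contrasts required.* Supported vs passive is null here, so a favourable significant result occurs in at most 2.5% of trials. The change-score simulation gives 2–3%, and 0% if the supported arm worsens.

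**4. Power of the contrasts at d = 0.25** (normal approximation): 0.25/0.157 = 1.595, so Φ(1.595 − 1.96) = 36% at 47 per arm; 0.25/0.136 = 1.832, so Φ(1.832 − 1.96) = 45% at 62. The two contrasts share the supported arm (correlation 0.5), so winning both has about 20% and 28% power.

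**The case against.** The strongest defence is that direction is present elsewhere in the article. The hypothesis is directional, and the sample size section speaks of supported monitoring against either control. The analysis section adds Cohen's d, responder and deteriorated classes, NNT and NNH, and Anticipated Results commits to examining harm. A worsened supported arm would be visible, and follow-up contrasts are detail that an article often leaves to an analysis plan. It stands that a careful analyst would look at the means. But none of these items conditions the conclusion. The rule is stated outright, so this is not an omission that an unseen plan would fill.

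The defence is also right that the percentages depend on assumed deterioration, and that the upper ones need four waves and no sphericity correction.

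Three stronger readings are tempting and are not supported:

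- A reader might infer that the trial has a very high false-positive rate. It does not when no arm differs: the simulated rate is about 5%. The problem arises when arms differ in the wrong way.
- A reader might add that chance differences between screening and baseline can trigger the rule. That is ordinary type I error, already covered by alpha.
- A reader might take 0.4 SD as the expected harm. The article gives no size.

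**Conclusion.** The rule is wrong as written. Read literally, it cannot tell benefit from harm, and it contradicts the article's own hypothesis. That conclusion needs no numerical assumption.

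The frequency of a wrong claim does. It assumes worsening of 0.25 to 0.4 SD confined to the AA arm and lasting to follow-up, equal correlations of 0.65, and complete data at the stated N. Under these assumptions the rule declares effectiveness in about 26–82% of trials at N = 141 and 34–92% at N = 186. The defect lies in the decision rule. An omnibus interaction can stay as a supportive test.

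**What to change.** Replace the sentence with a rule based on two prespecified contrasts of K6 at post-assessment, supported vs AA and supported vs passive, each adjusted for baseline (T1) K6. Conclude general effectiveness only if the supported arm is significantly better than both, each two-sided at 0.05. No further multiplicity correction is needed, because both must succeed. Report a win over AA alone as superiority to unsupported monitoring and not as effectiveness, with the AA vs passive contrast beside it. Keep the omnibus interaction as supportive.

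The rewording costs no data, since Trial Status says that recruitment had not begun. The cost lies in power. The stated 95% belongs to the omnibus test at f = 0.125 and does not carry over to the contrasts. Sample Size Calculation should restate power for each contrast and for winning both, and the sample size or the target difference then needs review. Baseline adjustment recovers a little at no cost (residual variance 0.70 to 0.58).

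A minor, separate point: the ANOVA is prescribed for every outcome, yet for the help-seeking behaviour items "a score of one indicates that help had been sought and a score of 0 that help had not been sought". A model for binary data, such as logistic GEE, suits these better.
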